# Comparing the Effects of Oral Contraceptives Containing Levonorgestrel With Products Containing Antiandrogenic Progestins on Clinical, Hormonal, and Metabolic Parameters and Quality of Life in Women With Polycystic Ovary Syndrome: Crossover Randomized Controlled Trial Protocol

**DOI:** 10.2196/resprot.8631

**Published:** 2017-09-29

**Keywords:** polycystic ovary syndrome, oral contraceptives, randomized controlled trial, progestin

## Abstract

**Background:**

Oral contraceptives (OCs) have been used as a first-line option for medical treatment in women with polycystic ovary syndrome (PCOS). Despite theoretical superiority of products containing antiandrogenic progestins compared to OCs containing levonorgestrel (LNG), the clinical advantage of these compounds remains unclear.

**Objective:**

The aim of this study was to compare the effects of OCs containing LNG with products containing antiandrogenic progestins including cyproterone acetate, drospirenone, and desogestrel on clinical, hormonal, and metabolic parameters and quality of life in women with PCOS.

**Methods:**

We conducted a 6-arm crossover randomized controlled trial with each arm including OCs containing LNG and one of those 3 OCs containing antiandrogenic progestins. The anthropometric and clinical manifestations and hormonal and biochemical parameters of participants were assessed at 6 time points including baseline, after washout period, and 3 and 6 months after intervention.

**Results:**

The study is ongoing and follow-up of recruited women will continue until 2018.

**Conclusions:**

This study will provide scientific evidence on comparability of OCs with the various progesterones that will assist in decision making taking into account cost effectiveness.

**Trial Registration:**

Iranian Registry of Clinical Trials IRCT201702071281N2; http://www.irct.ir/searchresult.php? keyword=&id=1281&number=2&prt=12869&total=10&m=1 (Archived by WebCite at http://www.webcitation.org/6tSP8FNWo)

## Introduction

Polycystic ovary syndrome (PCOS), the most common endocrine and metabolic disorder [1-3], which affects between 5% and 10% of reproductive age women [4,5], is characterized by chronic oligo-ovulation or anovulation and hyperandrogenism resulting in infertility, menstrual irregularities, hirsutism, acne, and alopecia [6,7]. PCOS is associated with an increased risk of metabolic disorders such as obesity, dyslipidemia, hyperinsulinemia, insulin resistance, and metabolic disturbances, which increase the risk of diabetes mellitus and cardiovascular disease [8-12]. Previous studies report that certain aspects of PCOS have negative effects on the health-related quality of life for these women [13,14].

Oral contraceptives (OCs) are frequently recommended as first-line medical treatment for the long-term management of menstrual disturbances and hyperandrogenism manifestations in women with PCOS who do not seek pregnancy [15-18]. The remedial effect of OCs is attributed to the suppression of pituitary gonadotropin secretion and a decrease in androgen secretion [19,20]; in addition, the estrogen component of these compounds increases circulating levels of sex hormone-binding globulin (SHBG), which decreases androgen bioavailability [1,21]. Moreover, the progestin component of some of the new generation of OCs inhibits 5α-reductase activity and acts as an antagonist at the androgen receptor level [21,22], theoretically resulting in an increase in antiandrogenic activity [23]. Despite theoretical advantages of OCs with antiandrogenic properties from compounds such as cyproterone acetate (CA), drospirenone (DRSP), desogestrel (DSG), and ethinyl estradiol (EE) compared to OCs containing levonorgestrel (LNG) [1,24], clinical advantages of these compounds remain unclear [25].

In addition to the antiandrogenic effect of OCs, their metabolic effect is one of the main issues in OC therapy in patients with PCOS [26]. In fact, some studies have raised concerns regarding the potential adverse cardiovascular and metabolic effects of OCs in women with PCOS [2,27-30], including worsening insulin resistance and glucose tolerance and potential adverse effects on lipid patterns. It is also unclear whether the metabolic effects of OCs on PCOS are reduced by the use of certain progestin compounds. Despite the theoretical antiandrogenic advantage of the new generation of OCs, their possible metabolic adverse effects may be a serious threat [31].

Several studies that assessed the effectiveness of OCs on clinical, biochemical, and metabolic profiles in PCOS patients have reported conflicting findings [1,10,15,16,32-35]. However, a limited number of studies have compared the effects of the various OC products on different aspects of PCOS; the majority of these studies did not assess effects of OCs containing LNG.

Accordingly, in this crossover randomized controlled clinical trial, we aimed to compare the effects of OCs containing LNG with products containing antiandrogenic progestins on the clinical, hormonal, and metabolic aspects and quality of life of reproductive-age women with PCOS.

We hypothesize that in PCOS patients, OCs containing antiandrogenic progestins including DRSP, CA, and DSG have no advantage over products containing LNG on the clinical, hormonal, and metabolic profiles of these women or on their quality of life.

## Methods

### Overview of Study Design and Procedures

This study is a single institution crossover randomized controlled clinical trial with 6 treatment groups (A, B, C, D, E, and F) that commenced in February 2016. Our study design was based on the Consolidated Standards of Reporting Trials (CONSORT) requirements [36]. The research team included a gynecologist, midwife, endocrinologist, epidemiologist, and statistician. The trial was conducted at the endocrinology clinic of the Research Institute for Endocrine Sciences (RIES) of the Shahid Beheshti University of Medical Sciences, Tehran, Iran. Figure 1 presents an overview of the study protocol. Participants were recruited through 4 primary sources: online through professional social networks and referrals from municipal health centers, private clinics, and the Tehran Lipid and Glucose Study (TLGS). The trial was conducted at an endocrine outpatient clinic.

Before entering the study, the purpose of the protocol was clearly explained to the patients and written informed consent was obtained from all women enrolled. All eligible patients were randomly assigned to treatment groups (Figure 2). Patients in each of the groups alternately received OCs containing LNG or a product containing antiandrogenic progestins including CA, DRSP, DSG, or EE for 6 months. There was a washout period of 6 to 8 weeks between the 2 treatments. Clinical, hormonal, metabolic, and quality of life assessments were assessed at the time of recruitment and again at follow-ups. Hence, each patient was assessed for clinical and biochemical measurements at 6 time points: before the first treatment (baseline 1), after taking the first treatment for 3 months, after taking the first treatment for 6 months, 6 to 8 weeks after stopping the first treatment (baseline 2), after taking the second treatment for 3 months, and after taking the second treatment for 6 months (see Table 1).

Baseline fasting (for at least 9 hours) blood samples were collected between days 3 and 5 of the spontaneous menstrual cycle or progesterone-induced menstrual bleeding. Follow-up visits for blood sampling and clinical assessment were performed at 3 to 7 days after using last tablet. All sera were stored at –80°C until the time of testing. Following completion of the study (samples and data collection), all data will be analyzed using Stata software (StataCorp LLC).

**Figure 1 figure1:**
[figure not shown]
Overview of study design.

**Figure 2 figure2:**
[figure not shown]
Consolidated Standard of Reporting Trials flow diagram of the study.

### Ethical Considerations

Approval was obtained from the ethics committee of Shahid Beheshti University of Medical Sciences, Tehran, Iran (ethics code IR.SBMU.PHNM.1395.649). The trial is registered at the Iran Registry of Clinical Trials [IRCT201702071281N2].

Written informed consent was obtained from eligible participants after the content was clearly explained to the subjects by the trial assistant. All research tools, including questionnaires, will be completely anonymous; a unique code will, however, be included in each form in order to manage further references. All information on participants will be securely stored and only accessible to authenticated trial team members.

### Participants

Women with PCOS (age range 18 to 45 years) were recruited at the endocrine outpatient clinic of the RIES of the Shahid Beheshti University of Medical Sciences, Tehran, Iran, by publicly advertising in the community or by referral from physicians or other clinicians. PCOS was diagnosed according to the 2006 criteria from the Androgen Excess Society (AES) (hirsutism or hyperandrogenemia and oligo-ovulation/ anovulation or polycystic ovaries with exclusion of other androgen excess or related disorders) [37]. Patients testing positive for secondary etiologies including hyperprolactinemia, thyroid dysfunction, Cushing syndrome, congenital adrenal hyperplasia, and virilizing tumors were excluded from the study. Inclusion criteria were normal fasting plasma glucose (<100 mg/dL), normal cardiometabolic system, and normal hepatic function; all patients were nonsmokers and had negative pregnancy tests before enrollment. None of the women had taken medications known to affect plasma sex steroids for at least 3 months before the study. None of the patients planned to become pregnant or had had contraindications with the use of OCs.

Exclusion criteria were history of use of anexogenous hormonal agent within past 3 months; systemic disease such as cardiovascular disorder, renal disease, or liver disease; endocrinopathies including diabetes mellitus, thyroid dysfunction, hyperprolactinemia, and Cushing syndrome; contraindications to OCs; use of any medication related to PCOS such as hormonal, insulin sensitizer, or antiandrogen drugs within the previous 3 months; willingness for pregnancy; smoking; or any serious side effects of contraceptive use such as thrombosis, jaundice, or hepatic disorders. We excluded current study participants if they were unable to actively continue the cooperation required due to sickness, pregnancy, etc. Patients could terminate participation in the study for any reason. Patients who discontinued intervention for ≥2 months were excluded from the analyses.

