The severity of acne was classified according to a grading system based on the number of lesions and their spread on the face, back, and chest: mild—comedones (clogged hair follicles often similar to pustules that do not have any inflammation) present; moderate—the number of erythematous and popular moderate lesions was from 10 to 40 or number of pustules was from 10 to 40 (especially on the face); moderate to severe—the number of multiple and numerous papules and pustules was from 40 to 100 often accompanied by comedones in numbers of 40 to 100 on the face, upper chest, and back; severe—nodulocystic acne with painful nodules or pustules frequently observed on the chest and face and accompanied by smaller papules, pustules, and comedones [41].

To diagnose androgenic alopecia in participants, we used the following classification, which was presented by Ludwig [42] in Germany:

Grade I: perceptible thinning of the hair on the crown limited in the front by a line situated 1 to 3 cm behind the frontal hair lineGrade II: pronounced rarefaction of the hair on the crown within the area seen in Grade IGrade III: complete baldness (total denudation) within the area seen in Grades I and II

In addition, we will assess the common side effects of OCs during and after follow-ups (Table 2).

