### Hormonal Assay

FSH and LH will be measured by immunoradimetric assay (IRMA) (Institute of Isotopes Co Ltd) using the Wallac Wizard gamma counter (GMI Inc); tT, A4, and DHEAS will be measured by enzyme immunoassay (EIA) (Diagnostics Biochem Canada Inc). SHBG will be measured by immunoenzymometric assay (IEMA) (Mercodia AB); all enzyme-linked immunosorbent assay (ELISA) tests were performed using the Sunrise ELISA reader (Tecan Trading AG); and FAI will be calculated using the formula [tT(nmol/L)×100/SHBG(nmol/L)].

Biochemical hyperandrogenemia will be identified if FAI, DHEAS, or A4 levels are in the upper 95th percentile (tT=0.89 ng/mL, A4=2.9 ng/mL, DHEAS=179 μg/dL, FAI=5.39) considering the women studied were not on any hormonal medication and had no clinical evidence of hyperandrogenism and menstrual dysfunction. Hyperandrogenism was determined as clinical hyperandrogenism and/or biochemical hyperandrogenemia [43].

Inter- and intra-assay coefficients of variation for all hormonal measurements will be defined.

**Table 2 table2:** A comparison of the common side effects of oral contraceptives in polycystic ovary syndrome patients.

Side effects	Type of treatment			
	OC^a^ containing LNG^b^	OC containing CA^c^	OC containing DRSP^d^	OC containing DSG^e^
Headache	x	x	x	x
Dizziness	x	x	x	x
Nausea	x	x	x	x
Vomiting	x	x	x	x
Breast pain/tenderness	x	x	x	x
Spotting	x	x	x	x

^a^OC: oral contraceptive.

^b^LNG: levonorgestrel.

^c^CA: cyproterone.

^d^DRSP: drospirenone.

^e^DSG: desogestrel.

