This study has limitations. Patients may drop out after the first intervention period and not receive a second treatment. This makes within-subject comparison impossible and is particularly important if withdrawal is related to side effects. We expect a considerable rate of loss to follow-up. To eliminate carryover effects, a washout period of 6 to 8 weeks was scheduled between treatments. Considering carryover effects of treatments across study periods can potentially distort the results obtained during the second treatment and the observed treatment effects will depend upon the order in which they will be received, hence we designed 6 treatment arms with different treatment orders. We intend to assess side effects of treatments. Considering our patients were diagnosed by AES criteria, our results may not be generalizable for those minor phenotypes diagnosed using Rotterdam criteria.

Finally, it is important to note that this project and its design are novel in the management of PCOS. If OCs containing LNG are as effective as OCs containing CA, DRSP, EE, or DSG without safety concerns, they may be recommended as a cost-effective first-line treatment for patients who suffer from the symptoms of PCOS. Therefore, we predict that the findings of this clinical trial will provide useful information for clinicians.

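### Women who leave because of illness, pregnancy or long discontinuation can drop out of a side-effect comparison that lists only six common complaints: too weak a basis for a finding of no safety concerns

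*Protocol article*

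**What the plan says.** All references are to the protocol article.

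- **Participants, women already in the study:** "We excluded current study participants if they were unable to actively continue the cooperation required due to sickness, pregnancy, etc".
- **Participants, analysis rule:** "Patients who discontinued intervention for ≥2 months were excluded from the analyses". No exception is made for safety data.
- **Participants, exclusion list:** the last item is "any serious side effects of contraceptive use such as thrombosis, jaundice, or hepatic disorders". The text does not say whether this means history before entry, events during the study, or both.
- **Clinical Assessment:** "we will assess the common side effects of OCs during and after follow-ups (Table 2").
- **Table 2** (under Hormonal Assay) is titled "A comparison of the common side effects of oral contraceptives in polycystic ovary syndrome patients". Its rows are headache, dizziness, nausea, vomiting, breast pain or tenderness, and spotting, for each of the four products.
- **Discussion, conclusion:** "If OCs containing LNG are as effective as OCs containing CA, DRSP, EE, or DSG without safety concerns, they may be recommended" as a first-line treatment.
- **Discussion, limitations**, on women who drop out after the first period: "This makes within-subject comparison impossible and is particularly important if withdrawal is related to side effects".

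**The concern.** Illness, pregnancy and stopping treatment occur after treatment has begun, and each may be a consequence of the product being taken. The article treats them as reasons to exclude the woman. It then compares products on six common complaints.

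A woman who stops because of a serious event or a pregnancy, and does not resume within two months, is outside the analyses under the stated rule. Her event also has no row in the one side-effect table shown. The women who leave may be those most informative about harm.

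At stake is the safety half of the trial's intended message. Effectiveness alone does not trigger the recommendation of LNG. The absence of safety concerns is a stated condition, and a reader would take a quiet side-effect table as meeting it.

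**Working it through.** **1. Follow a woman through the stated rules.**

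| Event on a study product | Rule in Participants | Row in Table 2 |
|---|---|---|
| Illness that prevents her continuing | Excluded as a current participant | None, unless it is one of the six complaints |
| Pregnancy that prevents her continuing | Excluded as a current participant | None |
| Thrombosis, jaundice or hepatic disorder | Excluded if the serious-side-effect item applies on study; under either reading, out of the analyses if she stops for two months or more | None |
| Stops for two months or more because of a listed complaint | Out of the analyses | The complaint has a row, but she is no longer counted; no row for stopping because of it |

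The two-month rule alone is enough for the point. It does not depend on how the thrombosis and jaundice item is read.

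**2. What the other outcomes cover.** The Introduction names metabolic and cardiovascular effects as the concern with oral contraceptives. HOMA-IR is a primary outcome. Blood pressure, fasting glucose, insulin and lipids are secondary, and all are scheduled at six time points. They bear on safety and could go against LNG. They do not record serious events, pregnancies or side-effect withdrawals, and women removed from the analyses are missing from them too.

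**3. Precision available at best.** The article gives no figure for safety. Its sample size gives the exposure:

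- 6 groups × 25 = 150, and 150 / (1 − 0.25) = 200, as stated.
- Every woman is due one six-month LNG period, so LNG exposure is 150 (completers) to 200 (all enrolled, if all reach that period).
- With an even split across the three comparators (an assumption), each has 150 / 3 = 50 to 200 / 3 ≈ 67 women.

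If no events occur among n women and all events are captured, the one-sided 95% upper bound on the risk per treatment period is 1 − 0.05^(1/n):

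| Product | n | Upper bound |
|---|---|---|
| LNG, all enrolled | 200 | 1.49% |
| LNG, completers | 150 | 1.98% |
| Each comparator, all enrolled | 67 | 4.37% |
| Each comparator, completers | 50 | 5.82% |

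**4. How likely a clean record is anyway.** Six months of LNG gives 150 × 0.5 = 75 to 200 × 0.5 = 100 woman-years. The article states no rate of serious events, so the annual rates r below are assumptions. The chance of no event on LNG is (1 − 0.5r)^n:

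| Assumed rate per 1,000 woman-years | n = 150 | n = 200 |
|---|---|---|
| 0.5 | 96.3% | 95.1% |
| 1 | 92.8% | 90.5% |
| 3 | 79.8% | 74.1% |
| 10 | 47.1% | 36.7% |

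An absence of serious events would be weak evidence even with full capture. Steps 3 and 4 describe the size of the trial. They do not measure what the exclusions cost, which cannot be computed from the article.

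**The case against.** A reader might infer that the favourable safety finding for LNG is guaranteed in advance, or that the count of serious events would be zero whatever the true rate. The document does not support either reading:

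- The metabolic and blood pressure outcomes, and the six complaints themselves, can go against LNG. The Discussion's recommendation is also conditional.
- The thrombosis and jaundice item closes a list made up mainly of entry conditions, such as prior hormone use, contraindications and smoking. It may mean history before entry. Against that, the list already excludes contraindications, cardiovascular disorder and liver disease, so a purely historical reading is partly redundant. The item is unclear either way.
- Excluding a woman who cannot continue is not the same as leaving her event unrecorded. The CONSORT flow diagram (Figure 2) is not reproduced in the text available and may give reasons for leaving.
- The rules apply to every product. Lost events could hide harm on a comparator as easily as on LNG.

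All of this stands and limits the point. It is also fair that a journal article may leave serious-event reporting to the full protocol, so the lack of such a section is no fault here. Table 2 is titled as covering common side effects, and the Discussion says that side effects will be assessed and concedes that withdrawal related to them matters.

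None of this removes the stated rule. The article does drop long discontinuers from the analyses without a safety exception, and its safety condition is wider than the comparison it shows.

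**Conclusion.** The point holds in a limited form. As written, the exclusions and the six-item table are too weak a basis for saying there are no safety concerns about serious events, pregnancies and side-effect withdrawals. The metabolic and blood pressure outcomes cover another part of the safety question and are not in dispute. Nothing shows that the result would be forced, or that it would favour LNG: information is lost, and the direction of any bias is unknown.

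Even with complete capture and no events, the data could exclude risks above only about 1.5% per LNG period (2.0% with completers) and about 4.4% per comparator period (5.8% with completers). These figures assume an even split across comparators and that all women counted start the period in question.

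This is an inexpensive improvement worth making, not a flaw that invalidates the trial.

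**What to change.** - **Clarify the criterion.** State in Participants whether the serious-side-effect item applies at entry, on study or both, and reconcile it with the sentence on current participants. No clinical stopping rule needs to change.
- **Separate efficacy from safety.** Say that the exclusions for non-continuation and for discontinuation of two months or more apply to efficacy analyses only.
- **Define the safety summary.** Report common side effects, serious events, pregnancies and withdrawals because of a side effect by product being taken, in all women who took at least one tablet of that product. This adds a few rows to Table 2.
- **Limit the conclusion.** Replace the general safety condition in the Discussion with the observed rates and their confidence limits.

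The cost is some wording, a few table rows and a more cautious safety statement. Treatment and sample size are unaffected. The Results section says follow-up is ongoing, and the Overview places analysis after data collection ends, so the change can be made before the analysis.

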### Interventions

In this study, patients were randomly assigned to treatment groups with interventions using different OC products:

Group A: first treatment—EE 30 µg + LNG 0.15 mg daily for 6 months; second treatment—EE 30 µg + DRSP 3 mg daily for 6 monthsGroup B: first treatment—EE 30 µg + DRSP 3 mg daily for 6 months; second treatment—EE 30 µg + LNG 0.15 mg daily for 6 monthsGroup C: first treatment—EE 30 µg + LNG 0.15 mg daily for 6 months; second treatment—EE 35 µg + CA 2 mg daily for 6 monthsGroup D: first treatment—EE 35 µg + CA 2 mg daily for 6 months; second treatment—EE 30 µg + LNG 0.15 mg daily for 6 monthsGroup E: first treatment—EE 30 µg + LNG 0.15 mg daily for 6 months; second treatment—EE 30 µg + DSG 150 µg daily for 6 monthsGroup F: first treatment—EE 30 µg + DSG 150 µg daily for 6 months; second treatment—EE 30 µg + LNG 0.15 mg daily for 6 months

All participants received EE 30 µg + LNG 0.15 mg as the standard treatment. To eliminate carryover effect of treatments, a washout period of 6 to 8 weeks was in place between 2 treatments (Figure 2). Interventions were performed by a trained midwife with the assistance of another person who was aware of the type of intervention.

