### Study Outcomes

Outcome measures were collected at 6 time points: before treatments, after washout period, and after 3 and 6 months of treatments (Table 1).

Only one person conducted clinical assessments of participants, and she was blinded to groups to minimize any assessor effects. Biochemical measurements were performed by an expert laboratory technician under the supervision of a laboratory sciences specialist.

In this trial, the primary outcomes were free androgen index (FAI) and homeostasis model assessment–insulin resistance (HOMA-IR). Secondary outcomes were modified Ferriman-Gallwey score (FG); acne; regularity of menstrual cycles; blood pressure; androgenic profiles including follicle-stimulating hormone (FSH), luteinizing hormone (LH), total testosterone (tT), SHBG, androstendione (A4), and dehydroepiandrosterone sulfate (DHEAS); metabolic profiles including fasting blood sugar (FBS) fasting insulin, HOMA-IR, triglycerides (TG), total cholesterol (TC), high-density lipoprotein cholesterol (HDL-C), low-density lipoprotein cholesterol (LDL-C); and quality of life assessed by Health-Related Quality of Life Questionnaire for Polycystic Ovary Syndrome (PCOSQ-50) [13].

**Table 1 table1:** Schedule of clinical and biochemical assessments.

Item		Baseline 1	At 3rd month of treatment	At 6th month of treatments	Baseline 2 (after washout period)	At 3rd month of treatment	At 6th month of treatment
**Demographic characteristics**		x					
	Age, marital, educational, and occupational status						

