### Statistical Analysis

Descriptive statistics will be reported appropriately; normality assumptions will be tested per case by Kolmogorov-Smirnov or Shapiro-Wilk tests. A crossover study is a longitudinal study type in which participants receive treatments in different phases. Therefore, we will use repeated measures which are correlated. We will use statistical analysis appropriate for correlated measures such as generalized estimated equations or repeated-measurement designs to find the differences between treatments. This will be done after finishing the second phase. In addition, in first phase of study, we will estimate between-group differences using generalized linear models. A washout period was taken into account although carryover effect (residual effect) will be tested at the beginning of the analysis via appropriate statistical tests like *t* tests presented by Fleiss [50]. Statistical analysis will be performed using the software package Stata version 12 (StataCorp LLC).

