## Discussion

This study presents a protocol for a crossover randomized controlled trial to compare the effects of OCs containing LNG with products containing antiandrogenic progestins including CA, DRSP, EE, and DSG on clinical, hormonal, and metabolic findings and quality of life of reproductive-age women with PCOS. To our knowledge, this is the first trial with crossover design to compare the effects of different OCs on various clinical and biochemical aspects of PCOS. Results of this study will empower clinicians with evidence-based recommendations regarding treatment options and follow-up duration.

Different approaches have been used to treat patients with PCOS. Use of OCs is one of the most common treatment options for improving clinical and biochemical findings of PCOS [21,51]. It is well known that improvement in clinical signs of PCOS usually begins after 3 to 6 months of therapy, but because hair follicles have a half-life of up to 6 months, lifelong therapy may be needed to prevent recurrence [16,52]. In this study, patients were treated with OCs for a 6-month period in each phase.

To minimize selection bias, we enrolled patients from different settings such as professional social networks and municipal health centers, private clinics, and from among participants of the TLGS. These settings were located in different districts of Tehran. All patients who met the eligibility criteria were included in the study. Adolescent and premenopausal patients were not included in the trial because of different clinical and hormonal statuses in these periods.

An important strength of this study is its crossover design, in which the interventions under investigation are evaluated within the same patients, eliminating between-subject variability [53]. We designed this study and its methodological issues such as allocation, blinding, flow diagrams, patient preference, and carryover effects based on guidelines reported in the CONSORT statement [36]. This clinical trial is a head-to-head trial that permits patients to receive multiple treatments; hence, it can express preferences for or against particular treatments.

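### The 6 to 8 week washout cannot be relied on to clear carryover from the Ferriman-Gallwey score, given the protocol's own figure for hair-follicle half-life

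*Protocol article*

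**What the plan says.** Under Interventions, the protocol article gives the purpose of the gap between treatments: "To eliminate carryover effect of treatments, a washout period of 6 to 8 weeks was in place between 2 treatments". The limitations part of the Discussion repeats it: "To eliminate carryover effects, a washout period of 6 to 8 weeks was scheduled between treatments". Neither sentence separates fast-changing outcomes from slow ones.

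Earlier in the Discussion, the case for long treatment rests on slow hair turnover: "because hair follicles have a half-life of up to 6 months, lifelong therapy may be needed to prevent recurrence". The same sentence says that clinical signs usually start to improve only after 3 to 6 months of therapy.

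Study Outcomes lists the FG score first among the secondary outcomes ("Secondary outcomes were modified Ferriman-Gallwey score (FG"). Table 1 schedules it at all six visits, including baseline 2 at the end of the washout.

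Three features bear on carryover:
- The Discussion concedes that carryover could affect second-period results, and offers reversed treatment orders in reply.
- Statistical Analysis adds a test: "carryover effect (residual effect) will be tested at the beginning of the analysis".
- Statistical Analysis also plans a parallel comparison: "in first phase of study, we will estimate between-group differences using generalized linear models".

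**The concern.** The protocol uses slow hair kinetics to justify long treatment but does not apply them to the washout. On its own figure, much of a first-period effect on hair could still be present when the second period starts.

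Carryover that is equal for both products goes into the period effect and does no harm. Carryover that differs between products biases the within-woman contrast, and it will differ if the products differ in their effect on hair. Reversing the order does not cancel it, because in each sequence a different product leaves the residue.

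What is at stake is the FG conclusion. A reader told that the washout was there to eliminate carryover, and then shown a non-significant carryover test, would take the crossover FG estimate as clean when neither fact establishes that.

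**Working it through.** **Inputs from the protocol article.** Washout 6 to 8 weeks; treatment periods of 6 months; hair-follicle half-life up to 6 months; 25 women per group after withdrawal. The article's totals reproduce: 6 × 25 = 150, and 150/0.75 = 200. The 200 enrolled give 200/6, about 33 per group. The article gives no figure for residual carryover, so there is none to reproduce.

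**Assumptions, not in the article.** Exponential decay of the effect on FG; half-life h of 6 months (the stated upper bound) or 3 months (an assumed lower value); a true product difference τ of 0.5 SD; within-woman correlation ρ of 0.5 to 0.7.

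**1. Washout against half-life.** 6 weeks = 1.38 months and 8 weeks = 1.84 months. 1.38/6 = 0.23 and 1.84/6 = 0.31.

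**2. Share of a first-period effect remaining.** At baseline 2, b = 0.5^(w/h), where w is the washout in months. At month 6 of period 2, e = b × 0.5^(6/h).

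| h | washout | b | e |
|---|---|---|---|
| 6 months | 6 wk | 0.853 | 0.426 |
| 6 months | 8 wk | 0.809 | 0.404 |
| 3 months | 6 wk | 0.727 | 0.182 |
| 3 months | 8 wk | 0.654 | 0.163 |

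**3. Effect on the month-6 crossover contrast.** The contrast is half the difference between the two sequences in (period 1 minus period 2).
- Raw scores: τ(1 − e/2), giving 0.787 and 0.798 of τ (h = 6), or 0.909 and 0.918 (h = 3). That is 8-21% too small.
- Change from each period's baseline: τ(1 + (b − e)/2), giving 1.213 and 1.202 (h = 6), or 1.273 and 1.245 (h = 3). That is 20-27% too large.
- Adjustment for period baseline with coefficient k: τ(1 + (kb − e)/2). The bias is zero at k = e/b, which is 0.5 for h = 6 and 0.25 for h = 3.

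**4. Power of the carryover test** (two-sided 5%, noncentral t, n per sequence).
- Period sums: effect 0.5e, standard error √(4(1+ρ)/n). Power is 5-7% at n = 25 and at most 8% at n = 33.
- Baseline 2 minus baseline 1: effect 0.5b, standard error √(4(1−ρ)/n). Power at n = 25 is 29-48% (h = 6) or 20-37% (h = 3).
- Baseline 2 adjusted for baseline 1: effect 0.5b, standard error √(2(1−ρ²)/n). Power at n = 25 is 37-54% (h = 6) or 26-42% (h = 3). The best case at n = 33 is 67%.

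So the test runs from almost no power to, at best, missing this carryover one time in three.

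**5. Is the first-phase comparison better?** Standard errors in SD units, n = 25 per group:
- Raw crossover: √((1−ρ)/25) = 0.141 (ρ = 0.5) or 0.110 (ρ = 0.7). Adding the bias τe/2 of 0.04-0.11 SD gives a root-mean-square error of 0.12-0.18 SD.
- First phase, adjusted for baseline 1: √((1−ρ²)(1/25 + 1/25)) = 0.245 or 0.202. Pooling the three LNG-first groups (25 v 75) gives 0.200 or 0.165.

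At the same correlation the biased raw crossover still has the smaller total error: at most 0.177 against 0.200 for ρ = 0.5, and at most 0.153 against 0.165 for ρ = 0.7.

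**The case against.** The best defence has four parts.

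First, the washout sentences state a purpose, not an achievement. The article also lists carryover among its limitations and plans to test for it. That is fair, and it softens the conflict. But the purpose is stated without exception in two places, and one outcome does not fit it on the article's own evidence.

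Second, the half-life is an upper bound for follicles, cited to support long therapy. It does not measure how a drug effect on FG fades. This stands: every percentage above is illustrative. What survives is that the washout cannot be relied on for FG, not that a known fraction remains.

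Third, how one secondary outcome will be interpreted is something a condensed article may leave to the analysis plan. This also stands. The point therefore rests on the stated washout rationale, not on missing detail.

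Fourth, a first-phase analysis is less precise. By normal approximation it detects a 0.5 SD difference in 53-70% of trials (71-86% if pooled), against 79-99% for the biased raw crossover. This stands too, and it rules out replacing the crossover analysis or making the FG conclusion conditional on the first phase.

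A reader might also infer that the bias favours the trial's hypothesis that antiandrogenic products "have no advantage over products containing LNG on the clinical, hormonal, and metabolic profiles of these women". The article does not support that. It does not fix whether or how the period baseline enters the model, and the bias runs either way, or vanishes, depending on that choice.

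**Conclusion.** The point holds as a minor one. The washout is presented as the means to eliminate carryover for every outcome, and the article's own half-life figure means it cannot be relied on for FG. If the products differ in their effect on hair, the FG contrast could be off by roughly 8-21% downward (raw scores) or 20-27% upward (change from baseline 2). Neither the reversed orders nor the carryover test excludes this. The sizes rest on exponential decay, a half-life of 3 to 6 months, a 0.5 SD difference, correlation of 0.5 to 0.7 and 25 to 33 women per group.

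Two further readings go beyond the document. One is that the primary outcomes, FAI and HOMA-IR, are also contaminated. The half-life statement concerns hair only, and nothing here shows whether those outcomes are free of carryover or not. The other is that the drug-free entry rule ("None of the women had taken medications known to affect plasma sex steroids for at least 3 months before the study") shows the washout to be too short. That rule concerns plasma sex steroids at entry and is no benchmark for hair: with a 6-month half-life, 3 months would still leave 0.5^(3/6) = 71% of an effect.

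**What to change.** 1. Under Interventions and in the Discussion, exempt hair outcomes from the statement that the washout is there to eliminate carryover.
2. State that a non-significant carryover test does not clear the crossover FG estimate.
3. Keep the crossover FG estimate. Beside it, report the first-phase FG comparison already planned under Statistical Analysis, adjusted for baseline 1, as a carryover-free sensitivity analysis, and discuss any disagreement. Do not make the FG conclusion depend on it.

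This needs no new visits or data, only wording and one reported comparison that is already planned. The price is a more cautious FG conclusion. The first-phase estimate has 2.0 to 3.4 times the variance of the raw crossover (0.200²/0.141² = 2.0 pooled at ρ = 0.5; 0.202²/0.110² = 3.4 unpooled at ρ = 0.7, from unrounded values), so the two may differ by chance and the text should allow for that.
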